Mindfulness facilitates the ability to shift attention to experiences purposefully, with a sense of acceptance (as opposed to trying to change or react to it).17 Active mechanisms of mindfulness (e.g., improved attention, emotion regulation, decentering)18-22 combined with the unique circumstances of HCT caregivers, suggest that approaching thoughts/emotions/sensations via mindfulness may convey benefits above and beyond what is found in other treatment approaches.23-25 Mindfulness has been associated with psychosocial benefits in other populations (e.g., decreased negative affect26-31 and stress32,33). To date, a few small-scale, single-arm studies have investigated mindfulness for the cancer patient-caregiver dyad with promising results.34-38 There have been no studies examining mindfulness for HCT cancer caregivers. Our multi-disciplinary team systematically developed a 6-week mindfulness-based intervention for allogeneic HCT caregivers – FOCUS (**F**ocusing **O**n mindfulness for **C**aregivers **U**nder **S**tress) – with input from caregivers and transplant team members. FOCUS spans the course of patient treatment, with session 1 occurring prior to transplant, sessions 2-3 taking place immediately following transplant, and sessions 4-6 occurring post-discharge. Pilot testing revealed that FOCUS was highly feasible and acceptable for allogeneic HCT caregivers and useful for managing stress.39 Significant decreases in negative affect and increases in mindfulness, post traumatic growth, and mental health symptoms were observed from baseline to end of treatment; findings were maintained through the 1-month follow-up.

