**Assessment Visits.** After informed consent, caregivers will complete a battery of baseline questionnaires and a hair sample will be collected for cortisol testing (100% of caregivers allowed us to take hair samples during the pilot study). We anticipate this process taking about 30-40 minutes for the caregivers to complete. After completing questionnaires, caregivers will schedule their 6 treatment visits. Patients will complete a brief demographic questionnaire and three measures to assess distress. This should take about 10 minutes for patients to complete.

The same assessments will be completed at baseline, end of treatment (~8 week post baseline), and at follow-ups. Hair samples will be collected again from caregivers at the 6-month assessment. Whenever possible, assessment visits will coincide with a clinic visit to decrease burden. As needed, questionnaires will be mailed, texted (link) or emailed to participants (e.g., 6-month visit). Caregivers will be compensated $25 for baseline, end of treatment, and the 2-month follow-up visits; they will be paid $50 for the 6-month follow-up. Patients will be compensated $20 at each assessment time point (4 total). As described in Section C.5.5., caregivers will be asked to complete a daily diary each evening that should take no more than 2 minutes to complete. Caregivers who complete at least 70% of daily diary questions will receive a bonus payment of $40 at the end of treatment assessment visit.

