Mindfulness will be measured via two self-report measures. The Mindful Attention Awareness Scale (MAAS) assesses trait mindfulness, specifically the attentional component, on a 6-point Likert scale.140 The Five Facet Mindfulness Questionnaire – Short Form (FFMQ-SF) assesses additional facets of mindfulness not measured in the MAAS on a 5-point Likert scale: Observing, Describing, Acting with Awareness, Nonjudging/Acceptance, and Nonreactivity.141 Importantly, both the MAAS and the FFMQ significantly increased from baseline to end of treatment, suggesting that FOCUS improved mindfulness as expected in the pilot study.

Self-efficacy will be measured via the Caregiver Self-efficacy Scale (CaSES), which measures caregivers’ confidence in their ability to manage the HCT patient on an 4-point Likert scale. Previous research in other populations has shown that MBIs impact self-efficacy,142-144 and we would expect increases in self-efficacy to ultimately impact caregiver health outcomes. The Duke Functional Social Support Questionnaire (FSSQ) will assess social support on a 5-point Likert scale.145Coping will be assessed by three 6-point Likert items regarding a self-assessment of ability to cope and one multiple response item of coping strategies that have been used.

*Daily Diary*. All caregivers will receive a daily diary prompt to answer 10 questions each evening via the study app. These questions will appear throughout the 6 weeks of caregiver treatment and should take no longer than 2 minutes to complete. Affect will be assessed using six items from the PANAS-X (i.e., stressed, overwhelmed, frustrated, drained, guilty, hopeful).146 Because mindfulness is a multi-dimensional construct, three items adapted from existing measures (MAAS, FFMQ, Toronto Mindfulness Scale) will assess the domains of attention, non-judgment, and decentering.140,141,147 Self-efficacy will be assessed via 1 question derived from the CaSES.

*Alcohol and Tobacco use*. At each assessment, all caregivers will answer four items assessing the quantity and frequency of smoking cigarettes and three items from the Audit-C assessing alcohol use.

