**Specific Aim 3**: Aim 3 is to evaluate putative mechanisms and moderators of FOCUS. Prospective mechanisms of lower perceived burden are higher mindfulness and self-efficacy, and lower stress and negative affect. The measure of these variables at 2 months (6 months for cortisol) post-treatment will be evaluated using the same approach described for the analyses in Aim 1.

These variables will also be assessed within the daily diary component of the study, which allows for 2 additional opportunities to assess mechanisms. First, the repeated, daily measures will be assessed using GEE for condition comparison with an emphasis on the main effect of condition (averaged over the multiple daily measures) and the condition x time interaction (diverging trajectories with the group differences increasing over time). Second, the repeated, daily measures of an active mechanism variable and the measures of burden at 8 weeks and 2 months will be entered into a structural equation model designed to evaluate whether or not changes in an active mechanism variable precede changes in burden. Mplus version

8.4 will be used for these models.149

Potential moderators (e.g., gender, age, relationship to patient, income, proximity to cancer center [defined as the mileage of home residence from Moffitt], baseline caregiver distress) of FOCUS on caregiver burden will be evaluated by adding to the GEE model for Aim 1 the moderator (e.g., gender) and its interaction with condition. A significant interaction will be further explored by testing differences in burden for each condition within appropriate subsets of the moderator (e.g., male and female).

**Data management**. Study data will be managed through REDCap (Research Electronic Data Capture), a data management software system supported and provided free by Moffitt. REDCap allows creation of customized, secure data management systems including web-based data entry forms, reporting tools, and a full array of security features including user and group-based privileges with a full audit trail of data manipulation and export procedures. Nationally, REDCap software is developed, enhanced, and supported through a multi- institutional consortium led by Vanderbilt University. The Project Manager, along with the Research Coordinator, will oversee creation of the database, questionnaires, and an automated messaging system.

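### The Aim 3 diary model enters burden only at 8 weeks and 2 months, so it misses burden change during treatment; baseline burden should be added and the precedence claim limited to the 2-month path

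*Protocol*

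**What the plan says.** The Specific Aim 3 paragraph of the statistical section describes a second use of the diary, in a structural model: "the repeated, daily measures of an active mechanism variable and the measures of burden at 8 weeks and 2 months will be entered into" it. The paragraph gives the question that this model should answer as "whether or not changes in an active mechanism variable precede changes in burden". It names no other burden wave for this model.

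The Daily Diary paragraph under Measures states: "All caregivers will receive a daily diary prompt to answer 10 questions each evening via the study app". It adds: "These questions will appear throughout the 6 weeks of caregiver treatment". The ten items are six on affect, three on mindfulness and one on self-efficacy. None measures burden.

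The Zarit Burden Interview is in the questionnaire battery. Assessment Visits says: "The same assessments will be completed at baseline, end of treatment (~8 week post baseline), and at follow-ups". Table 4 marks burden at baseline, end of treatment and both follow-ups. Baseline burden is therefore collected, but it is not named as an input to this model.

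**The concern.** To show that a change in mechanism comes before a change in burden, a model needs a burden change that it can place in time relative to the mechanism. As written, the model holds one burden change, and that change starts after the diary stops. Two paths could be read as the answer, and each has a weakness.

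- **2-month burden given 8-week burden.** The time order is right, but any burden benefit already reached by week 8 is absorbed by the conditioning.
- **8-week burden on the diary trajectory.** Without a starting value this is a level. Baseline burden adds noise, and it confounds the path if it is related to the diary predictor.

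At stake is the temporal part of Aim 3: a real mechanism acting during treatment could be missed, or differences present at baseline could be read as one.

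**Working it through.** **1. Sample size.** The protocol gives no power figure for this model. Its analysable sample is 270 × (1 − 0.30) = 189, or 63 per arm. Its Aim 1 power statements (above .80 for 0.56 at alpha .025 and for 0.51 at alpha .05) reproduce with a two-sample t-test at 0.808 and 0.811. I use n=189.

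**2. What is measured and what is entered.**

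| | Baseline | Treatment weeks | 8 weeks | 2 months |
|---|---|---|---|---|
| Zarit collected | yes | no | yes | yes |
| Zarit in the model | no | – | yes | yes |
| Diary | start day not fixed | daily | ended | no |

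**3. Assumed model for a mechanism acting only during treatment.** None of these values is in the protocol. B0, B8 and B2 are burden at baseline, 8 weeks and 2 months in SD units, S is the diary change, and e is standard normal:

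B8 = 0.6·B0 + b·S + 0.8·e; B2 = 0.7·B8 + 0.7·e.

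Approximate test: z = |coefficient| × √189 / residual SD, with √189 = 13.75; rejection ≈ Φ(z − 1.96).

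*2-month path given B8.* S has no coefficient after week 8 by construction, so rejection is about 5%. If S also acted after week 8 at -0.2 or -0.3, simulated power on this path was 56% or 90%.

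*8-week path, b = -0.2, S unrelated to B0.*
- Without B0 the residual SD is √(0.6² + 0.8²) = 1.0, so z = 0.2 × 13.75 = 2.75 and power is 79%.
- With B0 the residual SD is 0.8, so z = 2.75 / 0.8 = 3.44 and power is 93%.
- These are ceilings for an error-free S. With S estimated as a slope from 42 diary days (6 weeks × 7), simulation gives about **66%** without B0 and **86%** with it. The two agree: 66% corresponds to z = 2.37, and 2.37 / 0.8 = 2.97 gives 84%.

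*8-week path, b = 0 (no mechanism).*
- Slope unrelated to B0: about **5%**.
- Slope related to B0 at 0.2: the spurious coefficient is 0.6 × 0.2 = 0.12, so z = 0.12 × 13.75 = 1.65 and rejection is 38% for an error-free slope. Scaling for diary error by 2.37 / 2.75 = 0.86 gives z = 1.42 and 30%. Simulation gives about **29%**.
- Diary mean level as predictor, related to B0 at 0.2 to 0.4: simulation gives **33-84%**.
- With B0 in the model: about **5%** in each case.

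**4. Does baseline burden settle time order?** A separate simulation (n=189, 1,000 trials) had no mechanism effect, and burden drove next week's mechanism. Assumptions: weekly autoregression 0.85 for burden and 0.70 for mechanism, baseline correlation -0.4, burden reliability 0.85 or 1.0. False-positive rates for the diary slope:

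| Burden to next-week mechanism | 8-week path, no B0 | 8-week path, with B0 | 2-month path given B8 |
|---|---|---|---|
| 0 | 9% | 4-5% | 4-5% |
| -0.1 | 10% | 17-21% | 4-5% |
| -0.2 | 37-43% | 50-57% | 4% |
| -0.3 | 76-82% | 80-87% | 4-5% |

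Baseline burden removes confounding by starting level. It does not remove reverse causation, and under feedback it makes the 8-week path slightly worse. Only the 2-month path conditional on 8-week burden keeps its nominal error rate throughout.

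**The case against.** Several points on the other side stand.

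- **The 8-week-to-2-month change is of interest in itself.** Project Overview and Timeline says the 2-month visit is meant to capture gains since end of treatment, and the primary hypothesis is at 2 months. It is also the only interval that the diary strictly precedes. This stands, and is why the precedence claim belongs on that path.
- **The 5% figure is built in.** It assumes no effect after week 8. This stands: it shows what the path cannot see, not that the path lacks power in general.
- **Baseline burden could come in as a covariate.** The Aim 1 rules admit predictors of burden at 8 weeks or 2 months, and baseline burden would very probably qualify. But those rules are written for the estimating-equation model, and the sentence on the structural model does not carry them over. It names its burden waves.

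Three stronger readings are tempting, and the documents do not support them.

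- **That the plan will usually produce a false mechanism.** The high rates need the diary mean level as predictor, or reverse causation. The protocol speaks of changes in the mechanism. A slope unrelated to baseline burden gives about 5%.
- **That the pilot shows burden moves early and then holds.** The background does say that "findings were maintained through the 1-month follow-up", but it names negative affect, mindfulness, growth and mental health symptoms. Burden is not among them.
- **That the mechanism has no starting value.** Early diary days may lie near baseline, and mindfulness, affect and self-efficacy questionnaires are taken at baseline. The Table 4 heading for app data, which runs from baseline to end of treatment, is weak evidence of a conflicting diary start.

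**Conclusion.** The concern holds in limited form. The inputs named for the model leave out the burden change that happens while the mechanism is tracked, although a baseline score exists. This is a feature of a stated analysis, not detail left for later.

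The size depends on assumptions: a baseline-to-8-week burden coefficient of 0.6, an effect of -0.2 SD confined to treatment, and the diary slope as predictor. Under these, leaving out baseline burden costs about 20 percentage points of power on the 8-week path (86 − 66). The false-positive risk runs from none to substantial, according to how far the diary predictor is tied to baseline burden.

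A reader might infer that adding baseline burden would let the trial show precedence during treatment. It would not: burden is not measured between baseline and 8 weeks, so its timing there cannot be recovered. The point concerns one analysis within Aim 3.

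**What to change.** In Specific Aim 3, enter the baseline Zarit score as a predictor of both the diary trajectory and 8-week burden, so that the baseline-to-8-week and 8-week-to-2-month changes are both modelled. State that any claim of temporal precedence rests on the path from diary change to 2-month burden given 8-week burden. State that the baseline-to-8-week result will be reported as association.

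At most, also clarify when diary prompts start, so that the text on the diary window and the Table 4 heading agree. An earlier diary start is optional.

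Cost: no new data collection, one more variable in the model, a few sentences of text and a more modest conclusion.

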# STATISTICAL CONSIDERATIONS

### Data Management and Statistical Considerations

Descriptive statistics will be used to summarize and evaluate the distributions of all study variables. Transformations will be applied, as needed, prior to hypothesis testing. Missing data analyses will assess 1) prospective predictors of missingness that may influence interpretation and generalizability of results from hypothesis testing and 2) whether or not multiple imputation for managing missing data would be beneficial. Paired comparisons will be used to identify group differences, despite randomization, in demographics, clinical, and psycho-social variables that will then be included as covariates when testing hypotheses. Primary analyses for Aims 1 and 2 will use generalized estimating equations (GEE) with an identity link function, linear regression, and compound symmetry for the working correlation matrix. Advantages to using GEE, which fit population-averaged models, are to 1) assess changes in the outcome variable over time, 2) aggregate measures of the outcome variable across time to capture condition differences that may appear at different times for different participants, 3) assess primary hypotheses with targeted comparisons that incorporate data from all participants across multiple assessments, and 4) help effectively manage missing data by study completers under the missing at random assumption (MAR). The Holm method148 will be applied to control for experiment-wise error in the primary analyses, with alpha set at .025 for tests of FOCUS vs UC and set at .05 for FOCUS vs HL. Primary analyses will be performed using SAS version 9.4 (SAS Institute, Cary, NC).

**Power Estimates**: There will be 90 dyads randomized to each condition, with at least 63 per condition (30% dropout) expected at the 2-month assessment. PASS 16 was used to estimate power and effect size based on this sample size. Aim 1 hypothesizes that average caregiver burden will be lower in the FOCUS vs UC condition at 2 months. With alpha=.025, a two-sided test, and group n’s of 63, it is estimated that power

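### Significant moderators are to be probed within subsets, but four of the six named are continuous or ordered, so the step needs cut-points the protocol does not give and loses some precision

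*Protocol*

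**What the plan says.** The paragraph on moderators under Specific Aim 3 (Protocol, Data Management and Statistical Considerations) lists "Potential moderators (e.g., gender, age, relationship to patient, income, proximity to cancer center", the last "defined as the mileage of home residence from Moffitt], baseline caregiver distress". That makes six named moderators:

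- gender: binary
- relationship to patient: categorical
- age, mileage and baseline distress: continuous or scored
- income: ordered

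Each is examined by "adding to the GEE model for Aim 1 the moderator (e.g., gender) and its interaction with condition". The next step is then stated as: "A significant interaction will be further explored by testing differences in burden for each condition within appropriate subsets of the moderator (e.g., male and female"). The same rule covers all six moderators, and its only example is a binary one. The protocol gives no cut-point or rule for forming subsets of the other kinds. It also does not mention reading the condition effect from the fitted model at chosen moderator values.

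On sample size, the power paragraph says: "There will be 90 dyads randomized to each condition, with at least 63 per condition (30% dropout) expected at the 2-month assessment".

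**The concern.** Moderators are a stated aim, and this follow-up step is what would tell a reader which caregivers benefit. For gender, a subset is simply a category. For the four continuous or ordered moderators, a subset exists only after someone picks a cut. This has two consequences.

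- The answer depends on the cut. A median split and a split into thirds describe different groups and can give different conclusions from the same fitted interaction.
- If each test uses only the caregivers in its subset, information is discarded. A half has 31 or 32 per arm and a third has 21. A non-significant result among, say, the more distant caregivers may then reflect little more than the small numbers.

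The interaction model has been fitted to everyone by this point, so the same question can be answered without a cut and with a smaller standard error.

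**Working it through.** **Inputs.** 63 per arm at 2 months (power paragraph). Two-sided alpha of 0.025 for FOCUS vs UC and 0.05 for FOCUS vs HL. Detectable differences of 0.56 and 0.51 SD. The protocol has no figures for moderator or subset tests, so the following are assumptions: a normally distributed moderator, a linear interaction, two arms compared at one time point, and residual SD of 1.

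**The protocol's own figures.** Two-sample noncentral t with 63 per arm:

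- d = 0.56, alpha 0.025: power 0.808
- d = 0.51, alpha 0.05: power 0.811

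Both exceed the stated 0.80, so the power statement is not in error.

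**Standard error of the condition difference.**

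- Subset holding fraction f of each arm: SE = √[2/(63f)].
- Fitted interaction model, m SD from the moderator mean: SE = √[(2/63)(1 + m²)].

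To compare the same quantity, m is set to the mean moderator value of the subset: 0.798 for the upper half and 1.091 for the upper third.

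| Comparison | Subset SE | Model SE | Ratio |
|---|---|---|---|
| Half (f = 1/2, m = 0.798) | √(2/63 × 2.00) = 0.252 | √(2/63 × 1.637) = 0.228 | 0.905 |
| Third (f = 1/3, m = 1.091) | √(2/63 × 3.00) = 0.309 | √(2/63 × 2.19) = 0.264 | 0.854 |

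The model SE is therefore about 10% smaller for a half and 15% smaller for a third. In 8,000 simulated trials per setting, the model-to-subset ratio for halves was 0.89 to 0.91, and the two estimates agreed on average.

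**Detectable difference in a half at 80% power** (normal approximation):

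- alpha 0.025: 0.78 by subset, 0.70 by model
- alpha 0.05: 0.71 by subset, 0.64 by model

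Most of the rise from the whole-arm values comes from asking about part of the moderator range, and the model does not remove it.

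**The two-step procedure as planned.** Simulated with 63 per arm, a difference of 0.40 SD at the moderator mean growing by 0.30 SD per SD of moderator, and both steps tested at two-sided 0.05 (an assumption, since the protocol sets no level for moderators). The follow-up is the top third by subset t test, or the model contrast at 1.09 SD.

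| Quantity | Subset | Model |
|---|---|---|
| Interaction significant | about 37% | about 37% |
| Follow-up significant, given a significant interaction | about 86% | about 98% |
| Both significant, all trials | 0.37 × 0.86 ≈ 32% | 0.37 × 0.98 ≈ 36% (36-37% across runs) |

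Part of the conditional advantage arises because the model contrast uses the same interaction coefficient that passed the gate. The joint row is the fairer summary.

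**No effect anywhere.** A significant interaction together with a significant result at any of three upper cuts (median, top third, top quarter) occurs in about 2% of trials. The same event with model contrasts also occurs in about 2%.

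**The case against.** **Stronger readings the documents do not support.**

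- A reader might infer that trying several cuts inflates false positives. Ignoring the interaction test, the best of the three cuts does reject in about 10% of null trials. But the protocol probes only after a significant interaction, which holds the rate to about 2%, and model contrasts do no better.
- A reader might likewise take the ungated power, about 62% by subset and 77% by model, as the cost. Under the planned gate the difference is 32% against 36-37%.
- A reader might infer that cuts will be chosen after seeing the data. The protocol does not say so, and a statistical analysis plan that is not shown may fix them.

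**The case for leaving the text alone.** The only example is categorical, where subsets are suitable. The wording could be met by contrasts from the fitted model. How an exploratory interaction is probed is often settled in the statistical analysis plan. Subset means do not assume linearity, which has some value for mileage or income. At exactly 1 SD from the mean, the model estimate is no more precise than a median-split half: 1 + 1² = 2.00 on the variance scale, against 2.00.

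**What stands.** The loss is moderate, it affects only the follow-up, and the linearity trade-off is real. But the protocol has already chosen a method, and for four of its six named moderators that method requires cuts. Cut-points fixed in advance would remove the arbitrariness but would not recover the precision. The linear form is also what the interaction test assumes when such a moderator is entered as a single term.

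**Conclusion.** The point holds as a minor one. For age, income, mileage and baseline distress, the stated follow-up needs cut-points the protocol does not supply and gives up precision the fitted model already has. The model SE is about 10% smaller than for a median-split half and about 15% smaller than for an extreme third. In the scenario examined, this comes to about 4 to 5 percentage points in the chance of a significant interaction followed by a significant top-third result.

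These sizes rest on a normal moderator, a linear interaction, 63 per arm and a single time point. The power figures also rest on the assumed effect (0.40 SD at the mean, 0.30 SD per SD). A skewed moderator, as mileage may well be, would change them.

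The finding does not extend to error inflation. Nor does it touch the interaction test, which the protocol does not say is dichotomised, the stated power, or the primary comparison of burden at 2 months.

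**What to change.** In the moderator paragraph of Specific Aim 3, replace the subset rule with wording such as:

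*If the interaction with age, income, mileage or baseline distress is significant, the FOCUS minus comparator difference in burden will be reported with its 95% confidence interval from the fitted interaction model at the 25th, 50th and 75th percentiles of the moderator, with all caregivers included. For gender and relationship to patient, the difference will be reported for each category from the same model.*

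Under the assumptions above, the quartile estimates (m = ±0.674) have SE √[(2/63)(1 + 0.455)] = 0.215, and the median estimate has √(2/63) = 0.178.

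The cost is a few contrast statements in a model already planned, with no new data. The small downside is that the estimates rely on the linear interaction form already assumed by the interaction test.
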